### Eligibility criteria

Secondary school students (Forms 2–4) who can understand Cantonese are the target group as most daily smokers started smoking weekly at age 10–19 years [8]. Those with identified cognitive or behavioral problems that affect their ability to respond to questionnaires will be excluded.

### Sample size calculation

G*Power [22] was used based on a small-to-medium effect size on the primary outcome, i.e. number of smoker referred by secondary school students at the 6-month follow-up (d = 0.35), based on our team’s experience in smoking cessation projects [11–13]. Hence, to detect a significant difference in the number of smoker referred between the two groups with a significance level of 5% and power of 80%, a total of 260 secondary school students would be needed. Based on a conservative estimation, around 360 eligible secondary school students can be approached in each school. The response rate for previous workshops of a similar duration was around 8% conservatively [11, 23]. Hence, we expect to recruit 28 (360 × 0.08) students in each school. For cluster RCT, it is estimated that the intracluster correlation coefficients = 0.01, and the design factor = (1+(28–1)*0.01) = 1.27, then the sample size needed will be 331 (260*1.27). With an estimated 10% attrition rate at 12 months, the total sample size needed will be 368 students (331/0.9) with 184 students in each group. Thus, a total of 14 schools with 7 schools (184/28) in each group are needed.

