### Clusters and randomization

14 clusters (14 schools) will be randomized to the intervention or control group using a 1:1 ratio by a research assistant (RA) who is not from our team using an independent computerized randomization sequence process that can only be accessed by that RA to ensure allocation concealment. This RA will login to an online platform to perform randomization. Randomization sequences will be generated by the computer in randomly permuted blocks sizes of 2, 4, and 6. The RA responsible for recruitment will record the exact date and time of recruitment. Computerized time stamps and electronic logs of sent allocation will be used to ensure allocation concealment. The RA undertaking recruitment will be responsible for data collection and be blinded to the group assignment.

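### The stated 80% power overlooks that only 14 schools are randomised: at the protocol's own inputs a valid school-level comparison has about 75% power (about 77% if 28 students per school enrol)

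*Protocol article*

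**What the plan says.** All of this is in the protocol article. The Clusters and randomization section makes the school the unit of allocation: "14 clusters (14 schools) will be randomized to the intervention or control group using a 1:1 ratio".

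The Sample size calculation section works in five steps:

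1. The target effect is a standardised difference in the primary outcome, "number of smoker referred by secondary school students at the 6-month follow-up (d = 0.35").
2. The size for individual students follows: "with a significance level of 5% and power of 80%, a total of 260 secondary school students would be needed".
3. The cluster size is set: "we expect to recruit 28 (360 × 0.08) students in each school". With it, "it is estimated that the intracluster correlation coefficients = 0.01", which gives a design factor of 1.27, and "then the sample size needed will be 331 (260*1.27").
4. Attrition is added: "With an estimated 10% attrition rate at 12 months, the total sample size needed will be 368 students (331/0.9) with 184 students in each group".
5. The number of schools is obtained by division: "a total of 14 schools with 7 schools (184/28) in each group are needed".

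No step allows for the small number of randomised units, whether by a larger critical value or by added schools.

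**The concern.** A design factor rescales the variance of the difference between arms to allow for students in one school resembling each other. It leaves the reference distribution untouched. The 260 was found with a t distribution on 258 degrees of freedom, and that choice is carried unchanged through 331 and 368.

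The information on how much schools vary comes from 14 schools, so a test that holds its 5% level refers to 14 − 2 = 12 degrees of freedom. The larger critical value costs power that the calculation never pays for.

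The stated power for the primary outcome is therefore higher than the design gives. A reader who meets a non-significant primary result would take the chance of having missed d = 0.35 to be 20%, when it is nearer 25% under the section's own enrolment and retention targets.

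**Working it through.** **Inputs, all from the Sample size calculation section:** d = 0.35; 5% level; 80% power; ICC = 0.01; 28 students per school; 10% loss; 368 enrolled; 7 schools per arm. The section does not say whether the test is one- or two-sided. Two-sided reproduces 260 and one-sided gives 204, so two-sided is used.

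**Step 1: reproduce the stated chain.**
- Two-sample t-test, 130 per arm: noncentrality = 0.35 × √(130/2) = 2.822; 258 df; critical value 1.969; power 80.3%. The total of 260 is reproduced.
- Design factor = 1 + (28 − 1) × 0.01 = 1.27; 260 × 1.27 = 330.2, rounded up to 331.
- 331/0.9 = 367.8, rounded up to 368, or 184 per arm.
- 184/28 = 6.57, rounded up to 7 schools per arm.

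**Step 2: power on the school-level degrees of freedom.** With N students analysed in 14 equal schools:
- m = N/14
- DE = 1 + (m − 1) × 0.01
- noncentrality = 0.35 × √(N/DE)/2
- power from the noncentral t distribution with 12 df, critical value 2.179

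For the stated target, N = 331:
- m = 331/14 = 23.6
- DE = 1 + 22.64 × 0.01 = 1.226
- effective N = 331/1.226 = 269.9
- noncentrality = 0.35 × √269.9/2 = 2.875
- power = 75.2%

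A simulation of t-tests on school means (200,000 runs) gave 75.1%, with a false-positive rate of 5.0% under no effect. With the same noncentrality and individual-level degrees of freedom, power would be 81.8%. The degrees of freedom alone therefore cost between 6 and 7 percentage points.

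**Step 3: other enrolment and loss scenarios at ICC 0.01.**

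| Enrolled | Loss | Analysed | Per school | DE | Power, 12 df | Power, individual-level df |
|---|---|---|---|---|---|---|
| 368 | 10% | 331 | 23.6 | 1.226 | 75.2% | 81.8% |
| 368 | none | 368 | 26.3 | 1.253 | 78.6% | 84.9% |
| 392 (14 × 28) | 10% | 353 | 25.2 | 1.242 | 77.3% | 83.7% |
| 392 | 5% (assumed) | 372 | 26.6 | 1.256 | 79.0% | 85.2% |
| 392 | none | 392 | 28.0 | 1.270 | 80.6% | 86.6% |

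**Step 4: effect detectable with 80% power on 12 df.** d = 0.372 with 331 analysed and d = 0.362 with 353 analysed.

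**Step 5: sensitivity to the ICC.** The values 0.005 and 0.02 are assumptions; the article gives only 0.01. With 331 analysed and 12 df, power is 79.1% at ICC 0.005 and 68.0% at ICC 0.02. Most of the fall at 0.02 comes from the ICC and not from the degrees of freedom: with individual-level df it is already 75.0%.

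**The case against.** **The quoted 260 is correct, and so is each later multiplication.** This stands. Nothing is miscalculated. The fault is that a power figure derived for individual randomisation is carried over to 14 schools with only the variance adjusted.

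**The plan enrols more than 368.** Fourteen schools at 28 each is 392, and the 10% loss is given for 12 months, while the primary outcome is at 6 months, when fewer may have been lost. This stands in part and narrows the gap: 77.3% with the full 10% loss, 79.0% with an assumed 5%, 80.6% with none. It does not close the gap for the target that the section states, since 368 students with no loss at all give 78.6%.

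**The planned test may not use 12 degrees of freedom.** The Data analysis section names no school term. That does not rescue the figure. An analysis that ignored schools would escape the 12-df limit but would not hold the 5% level that the calculation assumes. The article may also leave the model's detail to a fuller document, so its silence is not counted as a fault here. It does mean that the restated power should say which kind of analysis it refers to.

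**The effect size is a judgement.** The section bases d = 0.35 on the team's experience, and a move to 0.36 or 0.37 lies within any reasonable uncertainty about it. This is fair, and it is why the point calls for a restatement and not a redesign.

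**A reader might infer a larger shortfall.** Putting the factor 1.27 together with 331 students gives 73.7% power and a detectable d of about 0.38. That pairs a factor for 28 per school with 23.6 per school, so it is not a consistent scenario. The individual-level comparator for that pairing is also 80.4%, so setting 73.7% against 82% to 84% would exaggerate the loss. Likewise, a reader might conclude from higher ICCs that the trial is badly underpowered, but the article gives no ICC above 0.01.

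**Conclusion.** The stated 80% power for d = 0.35 does not hold for the stated target. With 7 schools per arm, 12 degrees of freedom and ICC 0.01, power is about 75% for 368 enrolled and 331 analysed, and about 77% for 392 enrolled with 10% loss. It reaches 80% only if 392 enrol and almost none are lost. The shortfall thus runs from about 5 percentage points to nearly none, depending on enrolment and on loss by 6 months.

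The result assumes a two-sided test, equal school sizes, an approximately normal outcome and an analysis that accounts for school. Unequal school sizes would lower power further. The documents support a modest overstatement of power. They do not support a claim that the arithmetic is wrong or that the trial must be enlarged.

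**What to change.** Keep 14 schools and 368 students. In the Sample size calculation section, replace the 80% claim with a statement along these lines: at ICC 0.01, and with a school-level comparison on 12 degrees of freedom, 368 enrolled and 331 analysed give about 75% power for d = 0.35 (about 77% if 28 per school enrol and 10% are lost), or 80% power for d of about 0.36 to 0.37. Add that this power refers to an analysis that accounts for school.

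Power at one or two other ICCs, such as those in the working, may be added as a sensitivity note, labelled as assumptions. The cost is one less favourable figure in the text, with no further schools, students or data.

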### Intervention group (ASAs)

#### Phase 1: ASA recruitment

This involves establishing a network for smoking cessation in the community. It includes recruiting ASAs through secondary schools. Promotional leaflets will be designed and distributed to the two NGOs and other secondary schools.

#### Phase 2: Training program

The training program will involve **1) training workshops**, **2) hands-on sessions,** and **3) a smoker referral competition**.

*1*. *Training workshops*. A half-day workshop (Fig 3) will be conducted by an RA trained by our team to train ASAs. Each workshop will last for 3 hours in secondary schools, at a local University, or online (depending on the preference of schools). The workshops will be based on those implemented in our previous smoking cessation projects [6, 7, 11, 13]. Specifically, when teaching the AWARD model, we will focus on educating ASAs about the skills needed to assess smokers’ smoking status, readiness to quit, and nicotine dependence. Importantly, ASAs will be taught how to deliver a brief intervention using the AWARD model (lasting about a minute or slightly longer) (Fig 4) [11]. Information of YQL will be highlighted so that ASAs can invite smokers to call YQL in ‘***R***efer’ of the AWARD model [11]. Also in ‘***R***efer’ of the AWARD model, the ASAs will be trained with some safety tips by the RA, including 1) stay with the respective nursing students at all times during the outreaching sessions, 2) stay on main streets only and never go to alleys, 3) never reveal your identity cards/student cards/telephone numbers or other documents/numbers that reveal your identities, 4) report to nursing students if you feel unwell/ any discomfort, 5) introducing signals of discord, and 6) educating appropriate solutions dealing with signals of discord [24].

**Fig 3 pone.0313404.g003:**
[figure not shown]
The rundown of the workshop. A figure showing the details of the workshops’ rundown.

**Fig 4 pone.0313404.g004:**
[figure not shown]
Checklist of the brief interventions using the AWARD model. The template of a checklist for ASAs to use in each intervention delivery.

Each ASA will be required to pass an examination before proceeding to the hands-on sessions. This examination has been adopted in our previous projects [6, 7, 11]. It will first involve a written test asking ASAs about their knowledge of smoking consequences and AWARD model, then an oral demonstration in response to a case scenario of a smoker (role-played by nursing students). The examinations will be assessed by our RA and team members, with 50% as the passing mark. Those who fail will be required to rejoin the training workshops and retake the examination until a passing mark is obtained.

*2*. *Hands-on sessions*. ASAs will then be required to follow their assigned nursing students to implement the brief interventions to smokers in Hong Kong. Specifically, nursing students will bring their ASAs to the outreach activities (2 hours each) to supervise ASAs delivering brief interventions using the AWARD model when encountering smokers aged 25 or below smoking. Each ASA will follow their respective nursing student to four outreach activities and two counseling sessions (2 hours each). During the counseling sessions, ASAs will listen to how the nursing students deliver smoking cessation counseling and join the conversations by applying the AWARD model, offering ASAs opportunity to experience smoking cessation counseling. All ASAs will receive a certificate after completion of this phase.

*3*. *Smoker referral competition*. All ASAs will then be given a 6-month period to use the AWARD model to deliver brief interventions to refer smokers who are aged 25 years or below to YQL independently, without the help of nursing students. To ensure ASAs’ safety, they are asked to approach smokers via their social network including peer smokers, smokers in families and schools. Smokers are defined as those who smoked tobacco products (including electronic cigarettes) in the previous 30 days, as defined in YQL and other projects related to smoking [6, 11].

Near the end of the brief intervention with the AWARD model, ASAs will provide the contact of YQL and invite the smokers to call YQL. Those who successfully contacted YQL staff will be regarded as a successful referral case.

#### Intervention fidelity

To ensure consistency of the brief interventions, all ASAs will be asked to adhere to the intervention protocol and complete the checklist developed by our team (Fig 4) after each delivery of the brief intervention. Additionally, each ASA will be supervised by a trained nursing student. ASAs will be encouraged to share any difficulties in delivering the brief interventions to the responsible nursing student for discussion and feedback. During the competition, ASAs will also be recommended to consult our RA if they encounter any problems. This study will also include audit trial which is independent from our team members and funder.

#### Safety issues

A YQL staff will also be present in each outreaching activity to monitor the students and provide assistance when necessary. Both nursing students and ASAs will be given a contact of the PI for emergency contact.

#### Phase 3: Award presentation ceremony

10 award certificates will be given to the top 10 ASAs who deliver brief interventions using the AWARD model to the largest number of smokers (excluding smokers found with the nursing students). The champion will receive a HKD4000 book coupon. The first- and second- runner up will respectively receive HKD 3000 and HKD2000 book coupons. The remaining 7 ASAs will each receive a HKD1000 book coupon. The incentives are also expected to improve the adherence of this study.

### Control group

Secondary school students will be only required to attend a 3-hour training workshops with AWARD model in their schools or the University by our trained RA. The contents of the workshops are the same as that in the intervention group. However control group will not join the examinations, hands-on sessions, the smoker referral competition nor be given checklists for conducting the brief interventions with AWARD model.

### Data collection

After randomization, responsible teachers in schools will first be briefed by our RA about the purpose and protocol of the project. The schools will then distribute our promotional leaflets, information sheet and consent forms to students or parents depending on schools’ preferences. Consent forms with students’/parents’ telephone numbers will be returned to teachers if students are interested in joining the project. Eligible students will be informed by our RA via telephone that their participation will be voluntary and confidentiality will be maintained. They will also be notified about the details and schedule of the program activities.

The RA will contact the students in the intervention and control group at the start of training program (T1), at the end of training program (T2), and at 3 (T3), 6 (T4), and 12 months (T5) after the end of the training program by telephone to complete a set of questionnaires.

At T2, each ASA will submit a 300-word reflective journal. Responsible teachers in participating secondary schools, participating nursing students, ASAs, and responsible YQL staff will be randomly invited to complete a one-to-one semi-structured interview focused on implementation. The interviews will be conducted by an RA at T2 until data saturation is reached.

At T5, ASAs and nursing students will be interviewed about maintenance. Another RA who is not involved in this project will be asked to generate random numbers using a computer for random selection of participants for the interviews. All interviews will last for around 15–30 minutes and be audio-recorded in a room in our university or online (e.g., via Zoom) depending on the preference of interviewees. Based on the interview guide developed by our team, they will be asked about their overall experience, facilitating factors, barriers, and feasibility of implementing brief interventions using the AWARD model to smokers at T2. At T5, they will be asked about the maintained effects and components of the project. It is estimated that around 40 and 20 interviewees will be needed to reach data saturation at T2 and T5, respectively. Each interviewee will receive HKD$200 as a travelling allowance.

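### Students are recruited and consented after their school is randomised, so the number and kind of volunteers can differ between arms before the intervention starts

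*Protocol article*

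**What the plan says.** Under Clusters and randomization, "14 clusters (14 schools) will be randomized to the intervention or control group using a 1:1 ratio". The safeguards given there concern that step: "Computerized time stamps and electronic logs of sent allocation will be used to ensure allocation concealment". The same section adds: "The RA undertaking recruitment will be responsible for data collection and be blinded to the group assignment".

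Data collection sets out what follows. "After randomization, responsible teachers in schools will first be briefed by our RA about the purpose and protocol of the project". Next, "The schools will then distribute our promotional leaflets, information sheet and consent forms to students or parents". Completed forms "will be returned to teachers if students are interested in joining the project". A research assistant (RA) then telephones eligible students, and "They will also be notified about the details and schedule of the program activities". T1 is taken at the start of the training programme.

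On expected uptake, Sample size calculation says: "The response rate for previous workshops of a similar duration was around 8% conservatively". Applied to about 360 eligible students, this gives the planned 28 per school.

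Limitations of the study states that blinding cannot be achieved, without saying whose. It does not mention recruitment after randomisation.

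**The concern.** In a cluster trial, randomising schools balances the schools' whole student bodies in expectation. It balances the enrolled students only if enrolment does not depend on the allocation. Here each enrolment step comes after allocation and passes through teachers who have been briefed on the protocol, for two quite different programmes.

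The primary outcome is sensitive to who volunteers. It counts smokers referred to the Youth Quitline (YQL) by the end of the 6-month competition, and competition participants are asked to approach smokers in their own social network. Willingness to approach smokers, and knowing any, could affect both volunteering and the count. A difference between arms could then partly reflect who joined rather than what the programme did. Unequal uptake would also upset the planned cluster size and balance.

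**Working it through.** **1. The plan's own figures.** Inputs from Sample size calculation: d = 0.35, 5% significance, 80% power, intracluster correlation 0.01, 28 students per school, 10% attrition.

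- Two-sample t-test, two-sided: 130 per arm, total 260. Sidedness is not stated; a one-sided normal approximation gives 202, so two-sided fits.
- Design effect: 1 + (28 − 1) × 0.01 = 1.27. Then 260 × 1.27 = 330.2, rounded up to 331.
- Attrition: 331 / 0.9 = 367.8, rounded up to 368, or 184 per arm.
- Schools: 184 / 28 = 6.57, rounded up to 7 per arm.

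The sample size reproduces. The problem lies in the order of recruitment and changes none of these figures.

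**2. Order of events** (Clusters and randomization; Data collection): school allocated → teachers briefed → leaflets, information sheets and consent forms distributed → interested students return forms to teachers → RA telephones students → T1. Nowhere does the article place identification or consent of students before allocation, or describe recruitment material common to both arms.

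**3. What each arm involves.**

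| | Control | Intervention |
|---|---|---|
| Workshop | 3 h | 3 h |
| Examination | none | yes, retaken until passed |
| Hands-on sessions | none | (4 + 2) × 2 h = 12 h |
| Referral competition | none | 6 months |
| Prizes | none | HKD1000 to HKD4000 for the top 10 |

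**4. Room for selection.** 360 × 0.08 = 28.8 volunteers per school, so about 92% of eligible students do not join. If response varied with the programme over an assumed 4% to 12%, a school would yield 14.4 to 43.2 students and seven schools about 101 to 302, against 184 planned per arm.

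**5. What a difference between volunteers could do.** The documents give no figure for this, so the differences below are assumed. Take no true effect, an effective 130 per arm (331 / 1.27 / 2 = 130.3), and a pre-existing difference of b SD in the tendency to refer. Then SE = √(2/130) = 0.124, and the chance of a significant result is 1 − Φ(1.96 − b/SE) + Φ(−1.96 − b/SE).

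| b (SD) | Share of d = 0.35 | Rejection rate at nominal 5% |
|---|---|---|
| 0 | 0% | 5.0% |
| 0.05 | 14% | 6.9% |
| 0.10 | 29% | 12.7% |
| 0.15 | 43% | 22.7% |
| 0.20 | 57% | 36.4% |

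The calculation treats the outcome as the plan's sample size does, as a standardised mean difference. By symmetry, the rates are the same whichever arm the difference favours.

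**The case against.** **Disclosure of the arm.** A reader might infer that students learn their own arm's programme before they consent. The article does not say so. It says only that students hear what the activities are and when they take place, and that call comes after forms are returned. Knowledge at signing would have to come from the teachers, leaflet or information sheet, whose contents are not shown; nothing says the prizes are mentioned at recruitment. This limits the point to a risk. The risk remains: teachers are briefed before any form goes out, a truthful schedule must differ by arm, and the call appears to precede T1, so students could drop out selectively before baseline.

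**Blinded recruiter.** If the recruiting RA is truly blinded, that person cannot give arm-specific details. Several RAs appear in the article, and it is not clear that the one who briefs teachers or telephones students is the blinded one. The statement is also hard to square with the limitation that blinding is impossible. Even a blinded recruiter would not blind teachers or students.

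**Direction.** A reader might infer that keen students will be over-represented in the intervention arm. The documents do not support that: the prizes may attract, but the examination and 12 hours of sessions may deter.

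**Source of the 8%.** The rate comes from workshops of similar length, which resembles the control programme more closely. It is too strong to say that it fits control alone, since one of the two cited sources is the team's earlier study training girl guides to promote cessation in the community.

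**Existing protection.** Intention-to-treat analysis and multiple imputation are planned, but they act on students already enrolled and cannot correct who volunteered.

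**Conclusion.** The concern holds as a risk of differential recruitment. The order of events is explicit, the programmes differ sharply, expected uptake is low, and the stated concealment protects the allocation of schools only. Volunteers can therefore differ by arm in number and kind before the intervention begins, and the primary comparison can be biased in a direction that cannot be determined.

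The size is unknown. The range of 6.9% to 36.4% in place of 5% rests wholly on assumed differences of 0.05 to 0.20 SD and on the plan's intracluster correlation of 0.01; it shows sensitivity and does not predict the bias.

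A reader might try to size the bias from the 1% of participants who referred smokers in the earlier teen programme cited in the Introduction. The documents do not support that: the 1% belongs to a different programme, and it is a yes/no proportion while the primary outcome here is a count.

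**What to change.** **Schools not yet started.** Use one common leaflet and consent form describing both possible programmes. Close the consent list and complete T1, then have the independent RA release that school's allocation. Analyse everyone on the closed list as randomised. This needs an amendment and a short delay, but no extra staff or visits. Its downsides are some withdrawals once the arm is known and possible disappointment among controls. Recruitment was due to end on 31 December 2024 and the article appeared on 14 November 2024, so few schools may remain.

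**Schools already enrolled.**
- Adjust the primary analysis for T1 variables already collected, preferring those unlikely to be affected by knowledge of the allocation: age, sex and smoking status. T1 here was measured after allocation, so keep T1 practice and self-efficacy for a sensitivity analysis.
- Report numbers approached and consented by arm. Reach already records the number and proportion of students reached; the split by arm is the addition.
- State recruitment after randomisation as a limitation. Adjustment corrects measured imbalance only, and the variables named above do not directly measure how many smokers a student knows.

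These steps cost almost nothing.

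**Text.** State which RA briefs teachers, telephones students and collects data, and who is blinded to what, so that Clusters and randomization, Data collection and Limitations of the study agree.

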### Outcomes

The primary outcome will be the number of smokers who referred by secondary school students to YQL at T4 (at the end of the 6-month competition). Secondary outcomes include the reach, adoption, implementation, maintenance, and other effectiveness measurements.

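### The end of training that times T2 to T5 falls at different points in the two arms and is defined inconsistently, and the primary referral count has no stated start and no rule on supervised outreach contacts

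*Protocol article*

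**What the plan says.** All references are to the protocol article.

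- **Timing, both arms (Data collection).** Contacts fall "at the start of training program (T1), at the end of training program (T2), and at 3 (T3), 6 (T4), and 12 months (T5", and those after T1 are placed "at the end of training program (T2), and at 3 (T3), 6 (T4), and 12 months (T5) after the end of the training program".
- **Training, intervention arm (Phase 2: Training program).** "The training program will involve 1) training workshops, 2) hands-on sessions, and 3) a smoker referral competition".
- **Hands-on sessions (Phase 2).** "Each ASA will follow their respective nursing student to four outreach activities and two counseling sessions (2 hours each". An examination comes first, and students who fail repeat the workshop and resit until they pass. The calendar length of this block is not stated. The 6-month competition follows it.
- **Training, control arm (Control group).** "Secondary school students will be only required to attend a 3-hour training workshops with AWARD model"; the "control group will not join the examinations, hands-on sessions, the smoker referral competition nor be given checklists".
- **Primary outcome (Outcomes).** "the number of smokers who referred by secondary school students to YQL at T4 (at the end of the 6-month competition". No start of counting is given, and no referral period is described for controls.
- **Referral case (Phase 2, competition paragraph).** A smoker who succeeds in contacting Youth Quitline (YQL) staff counts as a successful referral.
- **Prize ranking (Phase 3: Award presentation ceremony).** Students are ranked by smokers given brief interventions, "excluding smokers found with the nursing students". Neither Outcomes nor Measurements applies this exclusion to the primary outcome.

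**The concern.** Every contact after T1 depends on one event, the end of training, and that event is not the same in the two arms. In controls it is the end of the workshop. In the intervention arm it is the end of the hands-on phase on one reading, or the end of the competition on another. Knowledge, attitudes, practice and self-efficacy at T2 to T5 are then compared at unequal intervals since the workshop that both arms attend.

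For the primary outcome the risk is that part of the T4 difference reflects when counting began, or referrals obtained beside a nursing student on outreach, rather than what students later do independently. Controls have no outreach, so any such contacts add to one arm only.

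**Working it through.** **The plan's own figure.** From Sample size calculation: d = 0.35, 5% significance, 80% power. A two-sided two-sample t-test needs 129.1, so 130 per arm and 260 in total. The design factor is 1 + (28 − 1) × 0.01 = 1.27; 260 × 1.27 = 330.2, so 331; 331/0.9 = 367.8, so 368. The figure reproduces, and nothing below changes it.

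**Contact times.** Count months from the workshop, and let h be the months taken by the examination and hands-on sessions (not stated).

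| | Control | Intervention, T4 = end of competition (Outcomes) | Intervention, competition inside training (Phase 2 as worded) |
|---|---|---|---|
| T2 | 0 | h | 6 + h |
| T3 | 3 | 3 + h | 9 + h |
| T4 | 6 | 6 + h | 12 + h |
| T5 | 12 | 12 + h | 18 + h |

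The two intervention columns cannot both be right: Phase 2 as worded puts T4 six months after the competition ends, and Outcomes puts it at that end. In neither column do the intervention contacts fall at the same time since the workshop as the control contacts.

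**Counting window for the primary outcome, intervention/control.**

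- From T2, with T4 at the end of the competition: 6/6 = 1.00.
- From the workshop, with T4 at the end of the competition: (6 + h)/6 = 1.08, 1.17, 1.33, 1.50 for h = 0.5, 1, 2, 3.
- From the workshop, Phase 2 as worded: (12 + h)/6 = 2.08, 2.17, 2.33, 2.50 for the same h.
- From T2, Phase 2 as worded: 6 months each, but the intervention window would lie wholly after the competition.

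**What this could do to the comparison.** This is illustration only; h and the referral rates are assumptions. Take Poisson counts and no true effect, with control mean m0 and intervention mean m1, so that d = (m1 − m0)/√((m0 + m1)/2).

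(a) Extra time alone, m1 = m0 × (6 + h)/6:

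- m0 = 0.01 per student per 6 months, h = 3: 0.005/√0.0125 = 0.045.
- m0 = 0.1, h = 1 to 3: d = 0.05 to 0.14 (at h = 3, 0.05/√0.125).
- m0 = 0.5, h = 1 to 3: d = 0.11 to 0.32 (at h = 3, 0.25/√0.625).

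(b) Supervised outreach counted, equal time, m1 = m0 + 4r for r referrals in each of four outreach activities:

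| m0 | r = 0.02 (adds 0.08) | r = 0.05 (adds 0.20) |
|---|---|---|
| 0.01 | 0.36 | 0.60 |
| 0.1 | 0.21 | 0.45 |
| 0.5 | 0.11 | 0.26 |
| 1.0 | 0.08 | 0.19 |

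The planning effect is 0.35. The Introduction reports that 1% of participants in an earlier programme referred anyone, so a low baseline is plausible. That figure is a proportion of participants in another programme, not a mean count in this one. Counts more dispersed than Poisson would make every d above smaller.

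**The case against.** A reader might infer that the T4 count does compare unequal exposure and so favours the intervention arm. The documents do not establish that. Outcomes ties T4 to the end of the competition, the abstract lists workshop, hands-on sessions and competition in sequence, and students receive a certificate when the hands-on sessions finish. The natural reading puts T2 at that point, and a T2-to-T4 count is then 6 months in each arm. A ratio above 1 needs counting to start at the workshop, which no section says. On this view the Phase 2 sentence is loose wording rather than evidence that T4 will be mistimed.

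Supervised contacts are also partly handled. The referral case is defined in the competition paragraph, where students act without nursing students, and Measurements logs smokers met in outreach and counselling under Reach. The prize exclusion concerns brief interventions delivered, not YQL contacts. Finally, the schedule figure is not shown, and a full protocol or SAP may define the window.

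Much of this stands: it rules out stating unequal exposure as a fact. It does not remove the point. No figure or SAP can make both statements about T4 true. The placement of the case definition hints at competition-only counting without imposing it. Logging a smoker under Reach does not keep that smoker out of the primary count. And even on the natural reading, the two arms answer the secondary scales at different times since the workshop.

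**Conclusion.** The concern holds in a limited form. Three things follow from the text shown: Phase 2 and Data collection contradict Outcomes on where T4 falls; T2 to T5 sit at different times since the workshop in the two arms on either reading; and the primary outcome states neither when counting starts nor whether supervised outreach referrals count.

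Unequal exposure and one-sided supervised contacts are possible consequences, not demonstrated ones. Their size depends on the hands-on duration and on referral rates, neither of which is given. Under the assumptions above, extra time alone is negligible at a very low baseline (d at most 0.05 at 0.01 referrals per student) and approaches the planning effect only with a long hands-on phase and a higher baseline. Counting supervised referrals matters more: at low baselines it could match or exceed d = 0.35 with no true effect. Because this governs the primary outcome and is cheap to settle, it should be settled before the outcome is analysed.

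**What to change.** 1. Reconcile Phase 2, Data collection and Outcomes so that, for timing, training ends with the hands-on phase. T2 is then before the competition and T4 is its end.
2. Schedule control T2 to T5 at the same elapsed time since the workshop as in the intervention arm, for example by fixing one planned workshop-to-T2 interval for all schools.
3. Define the primary outcome as unique YQL contacts attributed to the student in the same 6-month T2-to-T4 window in both arms. Exclude smokers met in supervised outreach or counselling sessions and report them separately under Reach.

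A 6-month window running from the workshop would not serve, because it would cut off the last h months of the competition.

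The cost is protocol wording and control calls that fall some weeks later. Control referrals made between the workshop and T2 go uncounted, as do those of the intervention arm in the same interval. No contacts or participants are added, and the 260, 331 and 368 stand.
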